#### Postoperative extubation

2.4.4

Patients are transferred to the PACU with endotracheal intubation, and 4 mg/kg of sugammadex is intravenously pushed within 10s upon PACU arrival. Extubation will be performed when all the following criteria are met: (1) the patient was fully awake and could perform simple commands; (2) the pharyngeal reflex, swallowing reflex, and coughing reflex were fully restored; (3) the patient’s voluntary respiration was regular, and the tidal volume was 6–7 mL/kg (ideal body weight); (4) SpO_2_ was greater than 96% on FiO_2_ of 0.4 or less and PETCO_2_ was less than 45 mmHg; (5) hemodynamic stability; (6) core temperature was 36.5 °C or higher; (7) no evidence of early surgical complications; (8) adductor hallucis muscle train-of-four ratio (TOFr, T4/T1) ≥ 0.9 (extubation criteria follow international expert consensus or guidelines. However, diaphragm may recover faster than peripheral muscles; a TOFr ≥ 0.9 at adductor hallucis does not fully guarantee complete diaphragmatic recovery. This is precisely the reason why we set up T1–30 min post-extubation for POCUS measurements to ensure as complete a recovery of diaphragmatic function as possible).

#### Quality of postoperative recovery

2.4.5

Quality of Recovery Scale-15 (QoR-15) scores were performed by specially trained nurse anesthetists on preoperatively (T0), 1st day postoperatively (T2) and 3rd day postoperatively (T3).

#### Safety assessment

2.4.6

Detailed documentation of adverse events during the perioperative process: intraoperative hypotension (SBP < 90 mmHg or less than 20% of basal value) and sinus bradycardia (HR < 50 bpm), hypertension (SBP > 180 mmHg or more than 20% of basal value) and tachycardia (HR > 100 bpm), and delayed awakening (90 min after discontinuation of drugs). Other rare anesthesia-related complications include myocardial infarction, unstable angina, new onset arrhythmias, pulmonary edema, heart failure, respiratory failure, pneumonia, stroke, venous thrombosis, pulmonary embolism, renal failure, hepatic failure, gastrointestinal hemorrhage, and more.

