#### Maintenance of anesthesia

2.4.2

Since there is some influence of anesthesia mode or drugs on diaphragm function, it is important to homogenize the anesthesia management (25). Using PCV-VG mode, two-lung mechanical ventilation sets tidal volume at 6 ~ 8 mL/kg (ideal body weight), with 50%FiO2 to maintain SpO2 ≥ 95% (routine 100% FiO2 avoided to reduce absorption atelectasis risk), and the 50%FiO2 is the minimum feasible concentration to maintain the target SpO2 in this ventilation mode. For one-lung mechanical ventilation, a protective lung ventilation strategy is applied: tidal volume set to 4 ~ 5 mL/kg, respiratory rate adjusted appropriately, PEEP at 3 cmH2O, FiO2 is titrated according to the principle of using the lowest feasible concentration to maintain SpO2 ≥ 90%, and FiO2 titrated to maintain SpO2 ≥ 90% (up to 100% only for persistent hypoxemia), and driving pressure limited to ≤15 cmH2O to ensure PETCO2 ranges 35–45 mmHg. Capnothorax pressure during RATS is maintained at ≤8 mmHg to minimize diaphragmatic compression effects, and after one-lung ventilation completion and before resuming two-lung ventilation, the standardized lung recruitment maneuver technique of sustained inflation is performed for all patients in both VATS and RATS cohorts (sustained inflation at 20–25 cmH2O for 10 s) to reduce atelectasis. Anesthesia was maintained with remifentanil (0.15–0.3 μg/kg/min), propofol (1–4 mg/kg/h) and dexmedetomidine (0.5 μg/kg/h), combined with inhalation of sevoflurane 1–2%, with the anesthetics titrated to maintain a BIS index between 40 and 60 (7, 26) and avoid hypotension or hypertension [defined as a greater than 20% decrease or increase in mean arterial pressure from baseline (27)]. Intermittent intravenous injections of rocuronium are used to maintain muscle relaxation. All patients are managed according to a standardized protocol of enhanced recovery after thoracic surgery.

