#### Primary endpoint

2.7.1

Incidence of PDD (DE values less than 10 mm or negative) at 1 day postoperatively.

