#### Secondary endpoints

2.7.2

(1) Incidence and severity of PPCs at 7 days postoperatively; (2) T0-T3 diaphragm function at different time points (DTF, DE and the difference of DE between T1/2/3 and T0). (3) NRS scores and Ramsay sedation scores at different time points. (4) QoR-15 scores at different time points.

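### Section 2.4.6 sets the relative blood-pressure adverse-event limits at 20% of baseline instead of a 20% change from it, and does not match section 2.4.2 (minor; wrong as written)

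*Protocol article*

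**What the plan says.** Section 2.4.6 (Safety assessment) opens with "Detailed documentation of adverse events during the perioperative process" and then lists the events. The first is "intraoperative hypotension (SBP < 90 mmHg or less than 20% of basal value". Its counterpart is "hypertension (SBP > 180 mmHg or more than 20% of basal value". Each has an absolute limb in SBP and a relative limb tied to the baseline value. Neither relative limb contains a word for decrease, increase, below or above.

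Section 2.4.2 (Maintenance of anesthesia) uses the same two terms when it describes what the anaesthetic should avoid, "defined as a greater than 20% decrease or increase in mean arterial pressure from baseline". That definition rests on MAP, is clearly a change from baseline, and has no absolute limit. It stands in the sentence on drug titration, next to "with the anesthetics titrated to maintain a BIS index between 40 and 60".

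Blood-pressure events are not endpoints. The primary endpoint (section 2.7.1) is "Incidence of PDD (DE values less than 10 mm or negative) at 1 day postoperatively". The secondary endpoints (section 2.7.2) start with "1) Incidence and severity of PPCs at 7 days postoperatively" and go on to diaphragm measures, pain and sedation scores and QoR-15. Section 2.10 lists perioperative adverse events among the data recorded.

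**The concern.** There are two separate faults.

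1. The relative limb in section 2.4.6 does not say what it must mean. A recorder who follows it to the letter compares SBP with one fifth of baseline.
2. Reading it as a 20% change still leaves two definitions of the same terms, on different pressures and with different limits. Neither section says that its definition applies only to its own purpose.

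At stake is how many hypotension and hypertension events are recorded, and whether a reader of the results can tell which rule produced the counts. Section 2.1 puts surgery between July 2025 and May 2026 and the article is dated March 2026, so some events may already have been recorded under this wording.

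**Working it through.** The plan gives no event rate or other figure to reproduce. The check is arithmetic on the definitions.

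**Inputs.** From section 2.4.6: SBP limits of 90 and 180 mmHg and the 20% relative limb. From section 2.4.2: a change in MAP of more than 20%. The documents give no baseline pressure, so baseline SBP is assumed at 100 to 160 mmHg, with 120/80 mmHg as the worked example. MAP is approximated as DBP + (SBP − DBP)/3, where DBP is diastolic pressure; this is also an assumption.

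**Step 1: literal reading.** Relative limit = 0.20 × baseline SBP.
- Baseline 100: 20 mmHg. Baseline 120: 24 mmHg. Baseline 160: 32 mmHg.
- Hypertension: at baseline 120, any SBP above 24 mmHg qualifies, so essentially every reading is an event and the 180 mmHg limb is redundant.
- Hypotension: the relative limb could add to the 90 mmHg limb only if 0.20 × baseline exceeded 90, that is at a baseline above 90/0.20 = 450 mmHg. It never acts.
- A reading of 80 mmHg from a baseline of 120 would count as hypotension (below 90) and as hypertension (above 24) at once.

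**Step 2: reading as a 20% change in SBP.** Limits = 0.80 × and 1.20 × baseline, combined with the absolute limbs.
- Baseline 120: below 96 or above 144 mmHg.
- Baseline 100 to 160: the effective lower limit runs from 90 to 128 mmHg and the upper limit from 120 to 180 mmHg. The definition now works.

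**Step 3: does Step 2 agree with section 2.4.2?** Assumed baseline 120/80, MAP = 80 + 40/3 = 93.3 mmHg.

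| Reading | SBP change | Section 2.4.6 (as 20% change) | MAP | MAP change | Section 2.4.2 |
|---|---|---|---|---|---|
| 100/60 | −16.7% | no event | 73.3 | −21.4% | hypotension |
| 95/75 | −20.8% | hypotension | 81.7 | −12.5% | neither |
| 146/80 | +21.7% | hypertension | 102.0 | +9.3% | neither |
| 140/105 | +16.7% | no event | 116.7 | +25.0% | hypertension |

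The two rules disagree in both directions, for both events. These constructed readings show that disagreement is possible. They do not show how often it would occur.

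**The case against.** The strongest reply is that this is a slip of wording whose meaning nobody would miss. The 180 mmHg limb would be pointless if any SBP above one fifth of baseline counted, and section 2.4.2 shows that the authors think in terms of a 20% change. This stands as to intent: a drafting error is by far the likeliest explanation. It does not remove the need to correct an operative definition that gives a wrong result when followed.

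A second reply is that a titration target and an event-recording rule serve different purposes and may legitimately differ. This also stands. Section 2.4.2 does not tell anyone to record an event by MAP. What is missing is a statement that the two definitions are meant to differ. Without one, the same terms carry two meanings.

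A reader might go further and infer that the recorded rates will be uninterpretable, or that hypertension will be recorded in every patient. The documents do not support this. The intended change is easily inferred, and for hypotension the 90 mmHg limb gives a countable event even on the literal reading.

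A reader might also infer that a comparison of VATS with RATS will be distorted, since capnothorax is used only in RATS. No such comparison of blood-pressure events is stated: they do not appear in the objectives, the endpoints or the sample size (sections 2.6 to 2.8), and section 2.9 names no analysis of them.

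**Conclusion.** The point holds as a minor error. The relative limbs in section 2.4.6 are wrong as written: at an assumed baseline SBP of 100 to 160 mmHg they set a limit of 20 to 32 mmHg, which nearly every reading exceeds and none usefully falls below. With the evident meaning put in, section 2.4.6 still differs from section 2.4.2 in pressure measure and in having absolute limits, so the same reading can be an event under one and not under the other.

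The consequence is limited to descriptive counts of intraoperative hypotension and hypertension. The primary endpoint, the secondary endpoints and the power calculation are unaffected. The literal limits depend only on the assumed baseline range, and any plausible baseline gives the same conclusion. The disagreement between SBP and MAP rests on assumed readings and an approximate formula, and its frequency cannot be estimated from the documents. No view is taken on which measure or limits are clinically right.

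**What to change.** 1. In section 2.4.6, word the relative limb of both definitions as a change from the baseline value.
2. Reconcile sections 2.4.2 and 2.4.6. Either use one definition in both, or state that section 2.4.2 is a titration target and that section 2.4.6 alone governs the recording of events. The sponsor chooses the pressure measure and the limits.
3. Apply the resulting rule to all patients, including those already enrolled, before events are tabulated. Where anaesthesia records hold the pressures, re-derive the events already recorded.

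The cost is a short wording change, plus some re-derivation from existing records. Step 3 has a limit: section 2.4.1 says that blood pressure is monitored, but the article does not say that intraoperative readings are kept for the study, so re-derivation may not be possible for every patient. Where it is not, the report should say which rule those counts were recorded under. The downside is that counts already recorded may change.

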#### Assessment of PPCs

2.4.7

Postoperatively, pulmonary complications from postoperative 1st day to 7th day were recorded by a supervising physician who was unaware of the diaphragmatic ultrasound parameters. According to European Perioperative Clinical Outcome (EPCO) definitions (6), PPCs were defined as respiratory-related adverse events occurring in the postoperative period, which mainly included: respiratory tract infections, respiratory failure, pleural effusion, pulmonary atelectasis, and pneumothorax, bronchospasm, aspiration pneumonia (Table 1). In addition, PPCs were categorized as mild, moderate, or severe using pragmatic severity grading (Table 2).

**Table 1 tab1:** Postoperative pulmonary complications (PPCs).

Complications	Definition
Respiratory tract infection	The patient is receiving antibiotics for a suspected respiratory infection that meets one or more of the following criteria: new or altered sputum, new or altered cloudy lungs, fever, and a white blood cell count of >12 × 109/L
Respiratory failure	Postoperative room air inhalation PaO2 < 8 kPa (60 mmHg), PaO2: FI02 ratio < 40 kPa (300 mmHg), or arterial oxygen saturation < 90% measured by pulse oximetry, requiring oxygen therapy
Pleural effusion	Chest radiographs show blunting of the rib-diaphragm angle, loss of clear contour of the ipsilateral hemidiaphragm in the upright position, evidence of displacement of adjacent anatomical structures, or (in the supine position) blurred shadows of one hemithorax with preserved vascular shadows
Atelectasis	Lung turbidity, displacement of the mediastinum, hilar or hemidiaphragm toward the involved area, compensatory hyperinflation of the adjacent non-atelectatic lungs
Pneumothorax	Air in the pleural cavity, no vascular bed around the visceral pleura
Bronchospasm	Newly recognized expiratory wheeze treated with bronchodilators
Aspiration pneumonia	Acute lung injury following inhalation of regurgitated contents

**Table 2 tab2:** Pragmatic severity grading criteria (severity grading).

Severity	Definition	Clinical processing needs
Mildly	Causes only temporary damage and usually requires no special treatment	May require observation or basic support only (e.g., oxygen)
Moderately	More serious complications, but usually not leading to permanent damage or functional limitations	Clinical intervention required (e.g., antibiotics, noninvasive ventilation)
Severe	Significantly prolonged hospitalization, resulting in permanent functional limitations or death	Requires aggressive treatment (e.g., mechanical ventilation, ICU admission)

Mild: transient postoperative hypoxemia requiring short-term oxygenation.

Moderate: pneumonia requiring intravenous antibiotic therapy that has not progressed to respiratory failure.

Severe: acute respiratory distress syndrome (ARDS) requiring tracheal intubation and ICU monitoring.

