### Study design

2.1

This was a non-randomized, single-center, prospective observational study conducted at the Affiliated Cancer Hospital of Guangzhou Medical University. One hundred and forty-eight patients who underwent elective pulmonary resection for lung disease between July 2025 and May 2026 were included. Figure 1 is the study timeline. Bilateral diaphragm function was monitored by ultrasound at 4 time periods, 1st day before surgery (T0), 30 min post-extubation in the Post-anesthesia Care Unit (PACU) (T1), 1st day after surgery (T2), and 3rd day after surgery (T3). This standardized T1 measurement window will be uniformly applied to all enrolled patients in the study. Diaphragm thickness at the end of inhalation (DTei), diaphragm thickness at the end of exhalation (DTee), and DE during voluntary calming respiration were recorded at each time period. The occurrence of patients’ PPCs was tracked and observed during the 7 day postoperative period, and related clinical variables were recorded, respectively. Figure 2 is the trial flow chart.

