#### Primary

2.6.1

To describe the incidence of postoperative diaphragmatic dysfunction (PDD) and explore its association with postoperative pulmonary complications (PPCs) after minimally invasive thoracic surgery (VATS and RATS).

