### Statistical analysis

2.9

Percentages will be calculated for dichotomous data and analyzed by the Pearson chi-square test or Fisher exact test. Continuous variables will be expressed as mean standard deviation (Mean ± SD) and median (ranging from 25th to 75th percentiles), and Student’s *t*-test was used for comparison between groups; The paired sample *t*-test is used for comparison of the same index. Propensity Score Matching (PSM) will be performed to balance baseline characteristics (e.g., age, BMI, ASA classification, tumor complexity) between the VATS and RATS groups (1:1 matching ratio, caliper width 0.2 SD) to mitigate selection bias. A baseline characteristics table will be added as Table 1 in the final manuscript, which will present the demographic, clinical and surgical-related baseline data of the VATS and RATS groups before and after PSM matching, so as to clearly show the balance effect of the matching process on the baseline characteristics between the two groups. Multivariate regression models will further adjust for residual confounding variables not fully balanced by PSM. Spearman and Pearson correlation analyses are used for the correlation analysis of normal distribution variables and non-normal distribution variables, respectively. Differences in diaphragmatic function parameters (DE, DTF) across multiple time points (T0–T3) will be analyzed using Linear Mixed-Effects Models (LMM) to account for within-subject correlation of repeated measures and robustly handle missing data. Differences in DEs at different times in the same subject were assessed by the Wilcoxon signed-rank test for matched data. Associations between postoperative DE reduction and clinically significant perioperative variables were analyzed using binary logistic regression analysis and reported as estimated crude advantage ratios and relative 95% CI. Similarly, binary logistic regression with stepwise variable selection (forward method) will be used to explore risk factors for PPCs, following the “Rule of Ten” (at least 10 events per candidate variable) to avoid model overfitting. To determine the predictive power of ultrasound parameters for PPCs, ROC curve analysis will be performed to validate the predefined PDD threshold (DE < 10 mm) rather than seeking a new cut-off, evaluating its discriminatory ability for PPCs. For the correlation analysis between diaphragmatic ultrasound parameters (DE, DTF) and ARISCAT scores, Pearson correlation analysis will be adopted if both variables conform to normal distribution, and Spearman correlation analysis will be used if the distribution is non-normal. On this basis, a combined predictive model for PPCs will be constructed by integrating ultrasound parameters (DE, DTF) and ARISCAT scores, and Net Reclassification Index (NRI) and Integrated Discrimination Improvement (IDI) will be used to quantify the improvement of the combined model in the discriminatory ability of PPCs prediction compared with the ARISCAT score single-factor model; the area under the ROC curve (AUC) of the single-factor model and the combined model will be further compared to verify the predictive efficacy of the integrated approach.

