
However, there are some limitations. For example, this is a single-center study that exclusively involves thoracic surgery; therefore, the generalisability may not be extrapolated. This is a non-randomized clinical study and selection bias may be present, which is mitigated by the inclusion of Propensity Score Matching (PSM) and multivariate covariate adjustment in the statistical analysis plan to balance baseline characteristics between the VATS and RATS groups. Additionally, we decided on a 7-day postoperative follow-up because most patients are discharged around 7 days after surgery. We acknowledge that limiting follow-up to the first 7 postoperative days may underestimate the duration or delayed impact of diaphragmatic dysfunction since postoperative diaphragmatic dysfunction has been reported in the literature to persist beyond the early postoperative period. We stopped POCUS monitoring at T3 (postoperative day 3) based on existing evidence (12, 24, 35) indicating that PDD reaches its peak within the first 72 h post-operatively and is most prominent within the first 3 postoperative days, with the dysfunction index tending to stabilize thereafter; moreover, early PDD (within 3 days) has been identified as a key predictor of subsequent PPCs including those developing at postoperative day 7 (7, 12), even those developing after day 3.

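### PPCs are counted from day 1, the day PDD is read, with no rule that onset follows the scan, so the PDD–PPC analyses cannot separate prediction from concurrent or reverse effects.

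*Protocol article*

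**What the plan says.** The outcome window is set in section 2.4.7: "pulmonary complications from postoperative 1st day to 7th day were recorded". The exposure is set in section 2.7.1: "Incidence of PDD (DE values less than 10 mm or negative) at 1 day postoperatively". Section 2.1 places scans before surgery (T0), 30 minutes after extubation (T1), on day 1 (T2) and on day 3 (T3).

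The two are then related to each other. The primary objective (2.6.1) is to describe PDD incidence and to "explore its association with postoperative pulmonary complications (PPCs) after minimally invasive thoracic surgery". Section 2.8 sizes the study on an OR of 3.0 for PDD predicting PPCs. Section 2.9 states: "To determine the predictive power of ultrasound parameters for PPCs, ROC curve analysis will be performed". It adds NRI and IDI for ultrasound combined with ARISCAT. The Discussion (section 4) gives the intended direction: "early PDD (within 3 days) has been identified as a key predictor of subsequent PPCs".

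Table 1 counts atelectasis, pleural effusion and pneumothorax among the PPCs. One listed sign of atelectasis is "displacement of the mediastinum, hilar or hemidiaphragm toward the involved area".

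No section sets a landmark, orders PPC onset after a scan, or says how a patient who already has a PPC at T2 or T3 is handled.

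**The concern.** Day 1 is both the day on which PDD is classified and the first day on which a PPC counts. Day 3 lies well inside the outcome window. Suppose a patient has atelectasis or an effusion at the T2 scan and an excursion below 10 mm. Under the plan this patient is a PPC case with PDD and adds to the evidence that PDD predicts PPCs. Yet the complication may have reduced the excursion, or both may have arisen together from the operation.

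The study means to support risk stratification and targeted prevention. For that use, the finding must be present before the complication. With overlapping windows, the odds ratio, the discrimination of the 10 mm threshold and the gain over ARISCAT could all partly reflect complications that were already there.

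**Working it through.** **1. Windows side by side**

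| Item | Time | Section |
|---|---|---|
| T1 scan | 30 min after extubation | 2.1 |
| T2 scan, defines PDD | day 1 | 2.1, 2.7.1 |
| T3 scan | day 3 | 2.1 |
| PPC counted | day 1 to day 7 | 2.4.7 |

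Only T0 and T1 precede the PPC window. The nearest safeguards do not address order in time. The section 2.2 exclusions cover preoperative pulmonary disease and direct transfer to the ICU while intubated. Blinding of PPC assessors (2.4.7, 2.5) prevents diagnostic bias, but not a physical effect of a PPC on excursion. Propensity matching (2.9) balances VATS against RATS.

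**2. The plan's own figure**

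Inputs from section 2.8: PPC 37%, PDD 30%, OR 3.0, alpha 0.05 (taken as two-sided), power 0.80, dropout 10%. Solving 0.7·p0 + 0.3·p1 = 0.37 with OR 3.0 gives p0 = 0.292 and p1 = 0.553. The Wald formula is

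N = (1.96 + 0.84)² · [1/(0.7·p0·q0) + 1/(0.3·p1·q1)] / (ln 3)² = 132.6, so 133.

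133/0.90 = 147.8, so 148. The stated sample size reproduces and is not in dispute.

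**3. Apparent OR when PDD has no effect on later PPCs**

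The article gives neither the share s of PPCs present at T2 nor the PDD prevalence among those patients. Both are assumptions here.

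*(a) PDD fixed at 25% in everyone without an early PPC, and at pe in those with one.*

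P(PDD | PPC) = s·pe + (1 − s)·0.25, and OR = [P/(1 − P)] / (0.25/0.75).

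- s = 1/3, pe = 0.60: P = 0.200 + 0.167 = 0.367; OR = 0.579/0.333 = 1.74.
- s = 1/2, pe = 0.60: P = 0.300 + 0.125 = 0.425; OR = 0.739/0.333 = 2.22.
- s from 20% to 50% with pe from 50% to 70%: OR 1.29 to 2.71.

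Overall PDD in the first two cases is 0.25 + 0.37·s·0.35, which is 29% and 31%, close to the planned 30%.

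*(b) Overall PDD held at 30% and PPC at 37%, with PDD prevalence q among early PPCs.*

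PDD in the remaining patients is b = (0.30 − 0.37·s·q)/(1 − 0.37·s), whether or not they later develop a PPC. So P(PDD | PPC) = s·q + (1 − s)·b and P(PDD | no PPC) = b.

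| s | q = 40% | q = 50% | q = 60% | q = 80% |
|---|---|---|---|---|
| 10% | 1.05 | 1.10 | 1.16 | 1.28 |
| 20% | 1.11 | 1.23 | 1.36 | 1.66 |
| 30% | 1.17 | 1.37 | 1.61 | 2.20 |
| 40% | 1.25 | 1.55 | 1.93 | 2.99 |
| 50% | 1.33 | 1.77 | 2.36 | 4.25 |

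The effect is small if few PPCs are early. It reaches the design OR only in extreme cells.

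**4. Power if only PPCs after T2 count**

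Start from 133 evaluable patients. Patients kept: n = 133·(1 − 0.37·s). Events: 133·0.37·(1 − s). PDD is kept at 30% and the OR for later PPCs at 3.0. The test is a two-sided 5% comparison of two proportions, split 30:70.

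| s | n | events | power |
|---|---|---|---|
| none removed | 133 | 49 | 0.81 |
| 10% | 128 | 44 | 0.79 |
| 20% | 123 | 39 | 0.77 |
| 30% | 118 | 34 | 0.73 |
| one third | 117 | 33 | 0.72 |
| 40% | 113 | 30 | 0.69 |
| 50% | 108 | 25 | 0.64 |

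**The case against.** A reader might infer that in patients with a day-1 PPC and low excursion the PPC came first, and that the odds ratio is therefore biased away from 1. The article does not support that. It scans at T1, and its Introduction describes intraoperative ways in which the diaphragm may be impaired. Low excursion at T2 may continue a dysfunction that preceded the PPC and helped to cause it. The overlap leaves the direction open. The figures in step 3 attribute all excess PDD among early PPCs to something other than an effect of PDD, so they show what could happen, not what will.

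A reader might also infer that the primary result is compromised. It is not: the primary endpoint is PDD incidence on day 1, PPCs are a secondary endpoint, and the objective is worded as exploring an association. Against this, the sample size rests on the PDD–PPC odds ratio, and sections 2.8, 2.9 and 4 use the language of prediction.

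Three further objections stand in part.
- The article does not say that T3 values enter the prediction models, so that part is conditional.
- Section 2.10 does not list PPC onset, but the case report form is not shown and may hold it.
- Hemidiaphragm displacement in Table 1 is a static sign, whereas DE is movement during quiet breathing. The shared anatomy does not show that the outcome definition contains the exposure; it only makes a physical link plausible.

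None of these supplies the missing time order between scan and PPC.

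**Conclusion.** The point holds as a matter of temporal ambiguity. The article itself fixes an outcome window that includes the exposure day, sets no order within it, and claims prediction of subsequent PPCs. As written, PPCs present at T2 count as predicted by the T2 scan, so the association and the ROC, NRI and IDI results cannot bear the predictive reading. The incidence of PDD is unaffected.

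The size cannot be determined from the document. It could be negligible (OR 1.05–1.28 with 10% of PPCs early and PDD of 40–80% among them) or substantial (1.74 with one third early, 2.22 with half early, PDD 60% against 25%). Every one of these figures assumes no true effect on later PPCs and rests on assumed shares. Neither a definite direction of bias nor a definite amount should be claimed. Without onset data, the authors could not settle the question afterwards.

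**What to change.** - **Section 2.4.7:** record the date and time of first diagnosis of each PPC. Enrolment runs from July 2025 to May 2026 and the article appeared in March 2026, so extract this from clinical records for patients already enrolled if it was not captured.
- **Section 2.9:** base predictive claims (odds ratio, ROC, NRI, IDI) on PPCs first diagnosed after the T2 scan through day 7, among patients PPC-free at T2. Relate any T3 values only to PPCs after T3. Report PPCs present at T2 separately. Show the all-PPC day 1–7 result alongside, labelled as an association without time order.
- **Supporting exposure:** PDD at T1 precedes the whole window and may be used in support, with the Discussion's own caveat that residual neuromuscular effects may lead to overestimated dysfunction at T1.

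The change costs a data item, some record review and revised wording. It also has three scientific costs:
- Fewer events leave power for OR 3.0 at about 0.79 to 0.64 for 10–50% early PPCs. This should be stated rather than met by more enrolment.
- Early PPCs truly caused by PDD drop out, so the landmark estimate answers a narrower question.
- PPCs present but undiagnosed at T2 will still count as later events, so the problem is reduced, not removed.
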